### Randomisation

Randomisation was performed by PE and MB on 1st of April 2022 (Month 0, see Fig. 4), and was made public on YouTube (see Supplementary Information, Additional file 1). Immediately after, the enrolled schools and teachers were informed by e-mail about the result of the randomisation process.

To ensure a balanced representation of grade levels across the intervention and control groups, stratified block randomisation in a 1:1 ratio was used (i.e., schools with participating classes in grade 4–6 and schools with classes 7–10 were randomised block wise in RStudio using the ‘dplyr’ and ‘readxl’ packages).

Due to the type of the intervention, it was not possible to blind the participants to group allocation. However, allocation levels will be coded before analyses and the analysts will not be informed about the codes before the final analyses have been performed.

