#### Outcome measures

*School-based and overall PA behaviours* will be measured with Axivity® AX3 accelerometers (see full pre-registered study description of the investigation of PA behaviours [51]). All acceleration data will be processed in Matlab (Version 9.9.0 R2020b, Mathworks Inc., Natick, Massachusetts, US), which includes resampling, generating ActiGraph counts [58], identification of non-wear, and summarising the subjects’ time spent in different PA intensity domains and with types of PA behaviour as running, walking, standing, and sitting. Non-wear periods is identified from both acceleration and temperature using the method described in the study by Rasmussen et al. [59]. Pupils should have valid data from at least one pre-intervention PA measurement.

*School motivation* is measured using the Academic Self-Regulation Questionnaire (SRQ-A) [60]. The SRQ-A is a domain-specific 32-item self-report questionnaire developed for measuring the level of autonomy relative to doing different types of schoolwork among pupils in late primary and lower-secondary school. In this study, the items from the homework domain are omitted as not every school in Denmark uses homework.

*Wellbeing* will be measured using two different scales, the overall score from the KIDSCREEN-27 questionnaire and the pro-social behaviour scale of the Strengths and Difficulties Questionnaire (SDQ). KIDSCREEN-27 is the 27-item version of the KIDSCREEN Health-Related Quality of Life (HRQoL) questionnaire which measures the subjective health, wellbeing, and health-related quality of life of children aged 8–18 years [61]. The pro-social behaviour scale of the SDQ measures resources and functioning in terms of social skills and competences of children aged 11–17 years [62, 63], although high reliability was reported for use in pupils aged 10 years in a similar EOtC intervention study [26].

*Academic achievement* will be measured with two scales measuring reading competence and math skills. Reading competence will be measured with the validated age-adapted text reading test (Tekstlæseprøve, Grade 3–7; Tekstforståelse Udsagn A [Text comprehension Statement A], Grade 8–10) by Hogrefe [64]. Math skills will be measured with the validated age-adapted mathematical basic skills test (MG, Matematik Grunglæggende [Mathematics Basics]) by Hogrefe [65].

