#### Sample size

Three classes were expected to drop-out during the intervention as per observations in the TEACHOUT study [38]. We further expected a sample size reduction by approximately 20% of the pupils due to drop-out and invalid accelerometer data (equivalent to four pupils per class). We expected an analytical sample of ~ 30 schools, ~ 51 classes, and ~ 867 pupils in total. The expected analytical sample allows 95% power to identify a small to medium effect size using a one tailed test (Cohen’s d = 0.374 95% CI [0.187,0.561]). Calculations accounted for intraclass correlations (ICC) derived from the TEACHOUT dataset of 0.046 within classes and 0.035 within schools. Power calculations were conducted using R package PowerUpR [66].

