#### Statistical analyses

Estimation of intervention effects (H1, H2, and H3 of Sub-study 1) will be computed using a ‘per-protocol’ analysis [67]. All classes in the intervention group not adhering to the classification of ‘regular EOtC’ (an average of > 150 min of weekly EOtC over the school year) and all classes in control group practicing too high amount of EOtC (average of > 150 min of weekly EOtC over the school year) will be excluded. These analyses will be complemented with sensitivity analyses, following the principle of ‘intention-to-treat’ [67] which will include all schools in the analyses irrespective of their adherence to the intervention or control condition.

Linear mixed models (LMM) will be used to analyse how post-test scores varies as a function of whether the pupils were assigned to the intervention or the control group while taking into account pre-test scores, sex, age, and random effects of classes and schools. Please, see the H1 and H2 pre-registration for further information on the pre-processing steps and statistical modelling used for these data [51]. The base model used to assess H3 (effects on school motivation, wellbeing, and academic achievement) will include baseline as a covariate and school and class ID as random factor, and group allocation as the fixed effect of primary interest. Follow-up stepwise modelling will be used to investigate the contribution of previously shown confounders, i.e. primarily the number of weekly EOtC sessions [26], age, and sex [23, 68, 69], to the base models. All sub-studies will be reported following the CONSORT statements and flowchart [70].

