### Data processing

All analyses will be processed in either RStudio or IBM® SPSS® Statistics with the level of statistical significance for all tests set to < 0.05.

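### The H3 base model omits the grade stratum used to randomise schools and leaves age and sex to stepwise entry, so its standard error may be too large; separately, two reading tests need a common scale

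*Protocol article*

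**What the plan says.** All references are to the protocol article.

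- **Randomisation.** Allocation was 1:1 in blocks stratified by grade level: "schools with participating classes in grade 4–6 and schools with classes 7–10 were randomised block wise". The stated purpose was balance of grade levels between the groups.
- **Sub-study 1, Statistical analyses, general sentence.** Linear mixed models compare post-test scores by group "while taking into account pre-test scores, sex, age, and random effects of classes and schools". For H1 and H2 the section then refers the reader to a pre-registration for the modelling detail.
- **Same section, H3.** "The base model used to assess H3 (effects on school motivation, wellbeing, and academic achievement) will include baseline as a covariate". The only other terms are random school and class effects and group. Age, sex and the number of weekly EOtC sessions are then considered by stepwise modelling on top of that base.
- **Sub-study 1, Outcome measures.** Reading is measured with different tests by grade: "Tekstlæseprøve, Grade 3–7; Tekstforståelse Udsagn A [Text comprehension Statement A], Grade 8–10". The maths test is described as age-adapted, without naming forms by grade.
- **Sample size.** The expected sample "allows 95% power to identify a small to medium effect size using a one tailed test", with "d = 0.374 95% CI [0.187,0.561" and intraclass correlations of "0.046 within classes and 0.035 within schools". **Data processing** has "the level of statistical significance for all tests set to < 0.05".

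**The concern.** A factor used to restrict randomisation should normally be in the analysis model. Stratified allocation balances grade level between the arms and so removes that source of chance difference. If the model has no stratum term, any remaining difference between younger and older grades stays in the school-level variance, and the model reports a standard error larger than the design's real one. The trial then forgoes precision that its randomisation has already secured.

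Two features of the H3 text add to this. The general sentence and the H3 base model disagree on whether age and sex are adjusted for, so a reader cannot tell which model gives the H3 result. Stepwise entry also lets the data settle the final covariate set, and it puts two baseline characteristics in the same step as the amount of EOtC delivered, which arises after randomisation.

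Reading raises a different question, of scale rather than precision. If scores from two tests are pooled with a single baseline slope, the slope and the pooled effect are hard to interpret.

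**Working it through.** **Inputs.** From Sample size: 30 schools, 51 classes, 867 pupils (1.7 classes per school, 17 pupils per class), class ICC 0.046, school ICC 0.035, 95% power, one-tailed. From Data processing: alpha 0.05. From Recruitment: 1.8 classes per school. Not given anywhere: the residual difference between strata (assumed 0 to 0.5 SD) and the split of schools between strata (assumed equal).

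**1. The plan's own figure.** For a three-level design with schools randomised 1:1 and K schools, J classes per school and n pupils per class:

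SE = √[0.035/(0.25K) + 0.046/(0.25JK) + 0.919/(0.25JKn)], MDES = (t₀.₉₅ + t₀.₉₅) × SE, df = K − 2 = 28, multiplier 3.402.

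- K = 30, J = 1.8, n = 17: SE = 0.1099, MDES = 0.374, interval 0.187 to 0.561. This matches the stated figures.
- With the 51 classes expected after drop-out (J = 1.7): SE = √(0.035/7.5 + 0.046/12.75 + 0.919/216.75) = 0.1119, MDES = 0.381, power at 0.374 = 0.947.

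The stated figure reproduces without any covariates, so it does not depend on the stratum.

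**2. Leaving the stratum out.** A residual gap of d SD between two equal strata adds d²/4 to the school-level variance that the model sees: SE(model) = √[0.1119² + (d²/4)/7.5]. Because allocation was stratified, the true SE stays at 0.1119. At an effect of 0.374, approximate power is 1 − Φ(t₀.₉₅,₂₈ × SE(model)/0.1119 − 0.374/0.1119).

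| Assumed gap d | Model SE | SE inflation | Approx. power without stratum |
|---|---|---|---|
| 0 | 0.1119 | 0% | 0.950 |
| 0.1 | 0.1133 | 1% | 0.947 |
| 0.2 | 0.1177 | 5% | 0.940 |
| 0.3 | 0.1246 | 11% | 0.926 |
| 0.5 | 0.1444 | 29% | 0.874 |

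With the stratum in the model, the same approximation gives 0.949 throughout. The one-sided error rate falls when the term is omitted: on this normal approximation, from 0.0445 with no gap to 0.029 at 0.3 SD and 0.014 at 0.5 SD. The test is conservative, not invalid.

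**3. Putting the stratum in.** It uses one school-level degree of freedom (28 to 27). If it explains nothing, MDES is 0.381 before and after. On a different reading, in which the stratum accounts for part of the stated school variance of 0.035 rather than adding to it, explaining 25%, 50% or 100% of that variance gives MDES 0.363, 0.344 or 0.302.

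**4. Reading tests, from the timeline.** Pre-test B is placed before implementation, around the randomisation of 1 April 2022. Implementation ran from August 2022 to June 2023, with the post-tests in Months 10 to 12. Pre- and post-test therefore fall in different school years, and pupils would normally have moved up a grade. If the test follows current grade, a pupil in grade 7 at pre-test has a baseline on one test and an outcome on the other. The change of test lies between grades 7 and 8, whereas the strata divide between grades 6 and 7, so a stratum term alone would not repair this.

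**The case against.** A reader might infer that no model in the trial adjusts for the stratum. The article does not support that. The H1/H2 modelling is referred to a pre-registration that is not shown, and the general mixed-model sentence already includes age, a close proxy for grade stratum. The finding can be established only for H3, whose base model is set out in the article. Even there age and sex are deferred rather than absent, and the two sentences can be read as a general approach followed by a specific base model. That reading is possible, but it still leaves the adjusted H3 model unsettled.

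A reader might also take the larger inflation figures as the expected loss. They are not. No residual gap is given in the article. Baseline is in the model and may absorb most of a stable grade difference. The ICCs are unadjusted and are not shown to apply to H3 outcomes; the reference to invalid accelerometer data suggests a calculation for physical activity. The percentages are illustrations and do not bound the loss.

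Finally, that pupils switch reading test is an inference. The article does not say which test a pupil receives at post-test, or whether raw or standardised scores are analysed, and an article may leave scoring to a fuller document. A change of named test is documented for reading only, one of the five H3 measures. This objection stands against calling the baseline adjustment wrong; it does not remove the need to settle the scaling.

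**Conclusion.** The concern holds for H3. The base model omits the factor by which schools were randomised and leaves age and sex to data-driven entry, at odds with the sentence before it. The consequence is a conservative standard error and some lost power; the effect estimate is not biased and the stated 0.374 is not in error. The inflation runs from about zero, if baseline absorbs the grade difference, through 1%, 5% and 11%, to 29% at an assumed residual gap of 0.5 SD, with equal strata and the plan's ICCs. For H1 and H2 an omission cannot be established. The reading-test issue is a separate scaling concern, conditional on the test following current grade.

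**What to change.** 1. In the H3 primary model, prespecify the randomisation stratum (grades 4–6 versus 7–10), age and sex as fixed effects alongside baseline, group and the random school and class effects, in place of stepwise entry for these terms. Align the general sentence with this.
2. Confirm that the pre-registered H1/H2 models include the stratum, and add it if they do not.
3. For reading, state which test each pupil takes at pre- and post-test. Analyse scores standardised within test and grade. If the test follows current grade, add a test-version term and its interaction with baseline for pupils whose test changes. Check whether the age-adapted maths forms need the same.

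The stratum costs one of 28 school-level degrees of freedom, with MDES still 0.381 if it explains nothing. Reading needs a standardisation step. No new data are required.

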Increased physical activity (PA) and decreased sedentary time reduces the risk of non-communicable diseases, such as cardiovascular diseases, diabetes, and morbidity over time [9]. Positive effects are also seen on wellbeing, cognitive functioning [10], and academic achievement during childhood [11]. European adolescents are far from reaching the PA guidelines, and activity levels decline with increasing age [12]. Furthermore, the decreasing levels of wellbeing and rise of mental health problems among adolescents has increased during the recent years [13]. Various attempts have been made to increase PA during school hours, e.g., through extracurricular activities such as active brain breaks or time slots allocated for movement activities [14, 15]. However, these approaches are often disconnected from school objectives, require additional manpower, or increasing workload for existing personnel and is not considered a primary objective by the teachers, which in many cases cause a low degree of implementation [16]. In contrast, ‘add-in’ approaches that integrate PA within primary pedagogical and didactical purposes have shown to achieve better adherence [7]. Education outside the classroom (EOtC) is be such an approach [17, 18].

EOtC has received widespread attention in the face of COVID-19 as a means to reduce school-based transmission [19]. Recent evidence suggests that EOtC in general, and perhaps even more so when conducted in nature, holds benefits for health and wellbeing [20–22]. Pupils have been observed to engage in more PA during EOtC compared to usual classroom-based teaching [23–25] as well as report higher school wellbeing [26, 27], school motivation [28], and academic achievement [29]. Therefore EOtC has been characterised [17, 18] as an intersectoral [30] and integrated ‘win-win’ opportunity for both health and education sectors, i.e., an ‘add-in’ approach to school-based PA promotion [7].

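### The H3 base model leaves out the grade-band stratum used at randomisation; if grade band still predicts the outcome after baseline adjustment, the test is conservative and some power is lost

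*Protocol article*

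**What the plan says.** Under Randomisation, the protocol article gives the aim and the method: "To ensure a balanced representation of grade levels across the intervention and control groups, stratified block randomisation in a 1:1 ratio was used". The strata are schools with participating classes in grades 4–6 and schools with classes in grades 7–10.

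Under Sub-study 1, Statistical analyses, three statements bear on the effect models:

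- A general sentence on linear mixed models relates post-test scores to assigned group "while taking into account pre-test scores, sex, age, and random effects of classes and schools".
- The H3 base model is then set out separately. It "will include baseline as a covariate and school and class ID as random factor, and group allocation as the fixed effect of primary interest".
- After that, "Follow-up stepwise modelling will be used to investigate the contribution of previously shown confounders". Age and sex are named there, with the number of weekly EOtC sessions.

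None of the three names the stratum or grade. For pre-processing and modelling detail the section points to a pre-registration, but only for H1 and H2.

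**The concern.** A factor that restricts the randomisation normally belongs in the analysis model. Balancing schools within grade band means that a difference between the bands adds nothing to the true sampling error of the arm contrast. A model without the band cannot know this. It counts the difference as unexplained variation between schools and charges it to the standard error. Intervals then come out too wide, the actual type I error falls below its nominal level, and power that the design has secured is not used.

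H3 is where the text shows the gap most clearly, because the article states the content of that model itself and does not defer it to another document. The pupils are aged 10–16, so some remaining difference between bands in motivation, wellbeing or achievement is possible. At stake is precision; the validity of a positive result is not threatened.

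**Working it through.** **Inputs.** From Sample size: 30 schools, 51 classes and 867 pupils (51/30 = 1.7 classes per school, 867/51 = 17 pupils per class); intraclass correlations 0.046 (class) and 0.035 (school); one-tailed test, 95% power, d = 0.374 with interval [0.187, 0.561]. From Recruitment and participants: 1.8 classes per school. From Data processing: alpha 0.05.

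**Step 1: reproduce the plan's figure.** For K schools, J classes per school and n pupils per class, with treatment assigned to schools and no covariates:

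SE² = 4(0.035)/K + 4(0.046)/(KJ) + 4(1 − 0.035 − 0.046)/(KJn)

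With K = 30, J = 1.8, n = 17: 0.004667 + 0.003407 + 0.004004 = 0.012079, so SE = 0.1099. With t(0.95; 28 df) = 1.701, the detectable effect is 2 × 1.701 × 0.1099 = 0.374, and 0.374 ± 1.701 × 0.1099 = [0.187, 0.561]. This matches the printed figure, so the stated power contains no stratum or covariate term.

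With J = 1.7, the stated analytical sample, SE² = 0.004667 + 0.003608 + 0.004240 = 0.012514, so SE = 0.1119 and power at d = 0.374 is 94.7%. This is the starting point below.

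**Step 2: what leaving out the stratum adds.** Let a share p of schools be in one band, and let the bands differ by δ SD after baseline adjustment. A model without the stratum adds p(1 − p)δ² to the school variance, and so 4p(1 − p)δ²/K to SE². The true sampling variance does not change, because allocation is balanced within band. The split of schools between bands is not given. Assume 16 and 14, so p(1 − p) = 0.249:

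- δ = 0.3: added 4 × 0.249 × 0.09/30 = 0.00299; SE = √0.01550 = 0.124
- δ = 0.5: added 4 × 0.249 × 0.25/30 = 0.00830; SE = √0.02081 = 0.144

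**Step 3: simulation of school means.** Same inputs, 1:1 allocation within band, 12,000 runs per setting, each analysed without and with the stratum term; one-sided alpha 0.05, power at d = 0.374.

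| δ (SD, assumed) | Mean SE, without / with | SE too wide by | Type I error, without / with | Power, without / with |
|---|---|---|---|---|
| 0 | 0.111 / 0.111 | 0% | 5.0% / 4.9% | 94.7% / 94.7% |
| 0.1 | 0.112 / 0.111 | about 1% | 4.9% / 5.1% | 94.6% / 94.8% |
| 0.2 | 0.117 / 0.111 | about 5% | 4.0% / 4.8% | 93.7% / 94.6% |
| 0.3 | 0.124 / 0.111 | about 12% | 3.2% / 4.7% | 91.8% / 94.5% |
| 0.5 | 0.145 / 0.111 | about 30% | 1.8% / 5.4% | 87.1% / 95.0% |

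The true standard deviation of the estimate stays near 0.112 in every row. An 18/12 split gives nearly the same standard errors (0.124 at 0.3 SD, 0.144 at 0.5 SD). In the top row the extra term costs no measurable power.

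**The case against.** The strongest reply is that the loss is hypothetical. No passage gives a grade-band difference for any H3 outcome after baseline adjustment, and at 0.1 SD or less nothing of practical weight changes. The 0.5 SD case adds 0.249 × 0.25 = 0.062 to a planned school variance of 0.035, nearly tripling it. This stands: the size is conditional. The high values are not excluded, since the intraclass correlations come from a study of grades 3–6 (Background) and so cannot contain a difference between grades 4–6 and 7–10. Nothing in the documents supports them either.

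Second, age is a close proxy for grade band. The general mixed-model sentence lists it and can be read as covering H3; otherwise the stepwise follow-up may bring it in. Either route would recover most of the loss. But the explicit H3 base model omits age, and a data-dependent step does not replace a prespecified design term. The text is best called ambiguous on age and silent on the stratum.

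Third, some stronger readings are tempting and do not hold:

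- **H1 and H2 have the same defect.** Age is listed for these models and their detail is deferred to a pre-registration that is not shown. It can only be asked whether the stratum is there.
- **The article itself shows that grade matters for H3.** Its remark that "activity levels decline with increasing age" is about physical activity, not motivation, wellbeing or achievement.
- **The change of reading test makes a stratum difference certain.** Outcome measures changes the test between grades 7 and 8, whereas the strata divide between grades 6 and 7. A stratum indicator would not capture the change. Both achievement tests are also described as age-adapted, which may shrink grade differences.

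Last, the main analysis is per-protocol and excludes classes by the EOtC they delivered, so the strata may not stay balanced and the table does not describe that analysis exactly. That is correct. It also gives a second reason for the term: if exclusions differ by arm and band, the stratum term would adjust for the resulting imbalance.

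**Conclusion.** The point holds for H3 in conditional form. The stated base model omits a factor that governed the allocation. If that factor still predicts the outcome after baseline adjustment, the standard error is too large and the test conservative. A reader might infer that the H3 intervals are too wide as matters stand, or that the results would be biased. The documents support neither: with no remaining difference there is no loss, and in no case is there bias or inflation of false positives.

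Over an assumed remaining difference of 0 to 0.5 SD, the excess in the standard error runs from 0% to about 30%, and the power loss at d = 0.374, one-sided, from nil to about 8 points (95.0% against 87.1%). At 0.2 SD the loss is about 1 point and at 0.3 SD about 3 points.

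These figures assume 30 schools of equal size, a 16/14 split between bands, all schools analysed, and planning intraclass correlations that apply to the H3 outcomes. They therefore fit the intention-to-treat analysis best. Severity: a minor efficiency improvement.

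**What to change.** Add the randomisation stratum (grades 4–6 or 7–10, coded as it was used at randomisation, including for any school with classes in both bands) as a prespecified fixed effect in the H3 base model, for both the per-protocol and the intention-to-treat analyses. State at the same time whether the general sentence listing sex and age also governs H3. Check that the pre-registered H1 and H2 models contain the stratum.

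The cost is one line in the plan and one of 28 school-level degrees of freedom. No new data are needed.

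### The covariate set for H3 is stated in two ways; the H3 base model leaves out age, sex and the grade band used in randomisation, which costs precision if outcomes keep an age trend

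*Protocol article*

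**What the plan says.** All statements on the H3 model stand in one section of the protocol article, Sub-study 1, Statistical analyses, which opens by naming H1, H2 and H3 together.

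- General sentence: mixed models compare post-test scores between groups "while taking into account pre-test scores, sex, age, and random effects of classes and schools".
- Next sentence: "Please, see the H1 and H2 pre-registration for further information on the pre-processing steps and statistical modelling used for these data".
- H3 model: a separate base model is named as the one for assessing H3. It "will include baseline as a covariate and school and class ID as random factor, and group allocation as the fixed effect of primary interest". Age and sex are not in it.
- Follow-up: "Follow-up stepwise modelling will be used to investigate the contribution of previously shown confounders", namely "primarily the number of weekly EOtC sessions [26], age, and sex [23, 68, 69], to the base models".

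The Randomisation section says that schools were allocated 1:1 in blocks, stratified by whether their classes were in grades 4-6 or 7-10. The H3 base model contains no term for that stratum. H3 covers five scales: SRQ-A, KIDSCREEN-27, the SDQ pro-social scale, reading and mathematics.

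**The concern.** Read as written, the section gives two covariate sets for H3: one with age and sex fixed, and one without them. An analyst following the protocol could fit either and claim to be on plan.

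The stepwise sentence also calls age and sex confounders. In a randomised comparison they are prognostic baseline variables, and age is closely tied to the randomisation stratum. The usual reason to include them is precision and a standard error that matches the stratified design. That reason does not depend on what a later modelling step shows.

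At stake is the width of the interval for the H3 group effect, and hence the power to detect an effect on motivation, wellbeing and achievement in pupils from grade 4 to grade 10.

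**Working it through.** **1. Anchor on the plan's own figure.** For a three-level cluster design with 1:1 allocation, SE² = 4[ρ_school/K + ρ_class/C + (1 − ρ_school − ρ_class)/N]. The Sample size section gives ICCs of 0.035 and 0.046, K = 30 schools, C = 51 classes and N = 867 pupils (17 per class). The detectable effect at 95% power, one-tailed 5%, 28 df, is 2 × 1.701 × SE.
- 54 classes, 918 pupils: SE 0.1099, effect 0.374, the stated value.
- 51 classes, 867 pupils: SE 0.1119, effect 0.381, close to it.

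The formula is therefore the right one. The stated 0.374 uses no covariates and is unaffected by this point.

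**2. Standard error with age and sex fixed.** Assume a baseline correlation of 0.6 (not in the document), which leaves residual variance 1 − 0.36 = 0.64. Then SE² = 4 × 0.64 × (0.035/30 + 0.046/51 + 0.919/867) = 0.00801, so SE = 0.0895. Pupil-level simulation gives about 0.091, which is used below.

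**3. Standard error with age omitted.** Assume one grade per school, grades 4 to 10 evenly spread (variance (7² − 1)/12 = 4), and a residual trend of b SD per grade. The omitted trend becomes school-level variance and adds 4 × b² × 4/30 to SE².

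| b (SD per grade) | Added to SE² | SE by arithmetic | SE, simulated base model |
|---|---|---|---|
| 0 | 0 | 0.091 | 0.090 |
| 0.05 | 0.00133 | 0.098 | 0.097 |
| 0.10 | 0.00533 | 0.117 | 0.115 |
| 0.15 | 0.01200 | 0.142 | 0.141 |

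**4. Why the base-model test is conservative.** Stratified allocation balances the two bands, so only grade variation within a band disturbs the comparison. That variance is (0.667 + 1.25)/2 = 0.96, not 4. The actual standard deviation of the estimate is √(0.091² + 4b² × 0.96/30) = 0.093, 0.098 and 0.106 for the three trends, which is smaller than the SE the model reports. With the two-sided critical value 2.048 (28 df), this predicts null rejection of about 3.0, 1.5 and 0.6%. Where no term is omitted, the same approximation gives 4.05%. The simulation with estimated variances (3000 runs each, sex effect 0.1-0.2 SD) gives 4.0, 2.4 and 1.1% for the base model, against 4.8, 5.2 and 4.6% with age and sex fixed.

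**5. What this does to power.** For a true effect of 0.25 SD (illustrative), power is approximately Φ((0.25 − 2.048 × SE)/actual SD).
- Age and sex fixed: Φ((0.25 − 0.186)/0.091) = 76%.
- Base model, simulated SEs: Φ((0.25 − 0.199)/0.093) = 71%; Φ((0.25 − 0.236)/0.098) = 56%; Φ((0.25 − 0.289)/0.106) = 36%.

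Simulation (1500 runs each) gives 76, 75 and 74% for the fixed model and 70, 57 and 36% for the base model.

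**6. Is the false-positive rate inflated?** A second null simulation (3000 runs per scenario, known variance components, nominal rate 4.05%) used standardised age slopes and sex differences of 0/0, 0.1/0.2, 0.2/0.3 and 0.4/0.4.

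| Rule | Null rejection, % |
|---|---|
| Age and sex fixed | 3.5, 3.9, 4.1, 4.2 |
| Model picked by covariate p-values | 3.6, 3.6, 4.1, 4.2 |
| Success if any of the four models (base, +age, +sex, +both) reaches p < 0.05 | 3.9, 4.6, 4.8, 5.3 |

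Even deliberate best-of-four picking adds only about 0.4 to 1.2 points over the fixed model.

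**The case against.** **The general sentence may cover H1 and H2 only.** The sentence after it points to their pre-registration, and H3 then gets its own model. This reading is possible, but the text does not say so, and the section opens with all three hypotheses. Even on this reading, H3 still omits age and the stratum.

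**The deciding model is named.** This stands. The base model is the one for assessing H3, group is its effect of primary interest, and the stepwise work is labelled follow-up. A reader might infer that each H3 scale gets several rival group-effect tests from which the best is taken. No sentence allows a follow-up coefficient to decide H3, and no entry or retention rule is stated, so data-driven selection is itself an inference.

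**Omitting age does not invalidate a randomised comparison, and the trend is assumed.** This also stands. The base model errs on the conservative side. Baseline score is already adjusted for and the achievement tests are age-adapted, so the residual trend could be near zero. The loss is then nil, but adding the terms would also cost almost nothing.

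**The exact modelling rule may sit in the full analysis plan.** That could excuse a missing rule. It does not excuse two different covariate sets in one section.

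**Conclusion.** The inconsistency is real: the H3 adjustment set is stated in two ways and must be reconciled. The consequence is lost precision and a reported standard error that is too large for the stratified design. It is not a false claim of effect.

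Under an assumed residual trend of 0.05 to 0.15 SD per grade, the SE is about 0.097 to 0.141 instead of about 0.091. The base-model test rejects about 1 to 4% under the null. Power for an illustrative effect of 0.25 SD falls by about 6 to 38 points. These sizes rest on assumptions the document does not supply: baseline correlation 0.6, one grade per school, grades spread across 4 to 10, and a two-sided 5% test. With no trend there is no difference.

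A reader might conclude that the stepwise step pushes the error rate clearly above 5%. The documents do not support that: the base model is designated, and the pupil-level calculations put the inflation at about 0.4 to 1.2 points even if the best of four models were chosen. The number of weekly EOtC sessions, listed in the same sentence, is a different matter because it is measured after randomisation. This point does not rest on it.

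**What to change.** State one H3 model, the same for all five scales: baseline score, age, sex, grade-band stratum and group as fixed effects, with school and class as random effects. Say that the group effect from this model decides H3. Reword the general sentence so that it agrees with this model or is expressly limited to H1 and H2. Remove age and sex from the stepwise step.

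The change is wording only. The general sentence already calls for age and sex, and the grade band is known from the randomisation. The price is a few degrees of freedom, some of them at school level because age and grade band vary mainly between schools. Going from 28 to 26 df, for example, moves the two-sided critical value from 2.048 to 2.056, which is negligible beside the possible gain.
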